### Analysis

Separate analyses will be undertaken for each of the study objectives.

#### Effectiveness

Linear mixed effects models will be used to analyse data related to the primary outcome with time-point (time since trial start) and time since intervention as factor variables. This allows for the expected nonlinear change over time, as well as an analysis of persistence of intervention and time-averaged intervention effects following the service redesign, consistent with recommendations.^40^ Generalised linear mixed effects models will be used to analyse the secondary outcomes (binomial for proportions and negative binomial for counts to allow for over-dispersion). A random effect for the clinic will be used for all models to account for clustering. Visual diagnostics will be used to assess model assumption validity, and transformations of outcomes or robust estimators will be used as needed. Adjusting for and analysing the association between covariates (eg, referral source and demographic data, including potential indicators of disadvantage such as need for interpreters) and outcomes will also be completed by including these in the mixed-effects models as predictors. Given the small number of clusters, the Kenward-Roger small-sample correction will be used for the df for inference of the fixed effects.^41^

In the event of any system-wide (eg, pandemic) and within-cluster notable disruptions (eg, staffing issues) that are not adequately captured by the baseline random-effects structure and residual variation, a disruption indicator variable will be used for the disrupted time period. This model of adjustment to disruption can also be included as an indicator within affected clusters only. As an additional sensitivity analysis, within-cluster time-series analyses will be conducted to account for localised temporal disruptions while assessing the persistence of intervention effects. R V.4.4.1 (or a newer version if available) will be used for the analyses.

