### Inclusion criteria

Included services (clusters) will be medical specialties (n=8) offering outpatient clinics at Eastern Health that have waiting lists with a minimum average of 12 weeks’ waiting time to first appointment and/or more than 200 people without appointments allocated. Given that referrals to a given specialty enter through a single waiting list but can then be distributed across multiple clinics (eg, operating at different locations across the health service), the clinics operating under each specialty will collectively form one cluster in the trial. Cluster selection will be decided in consultation with the medical directors of the clinics and senior leaders of the programme responsible for delivery of specialist medical clinics, based on (i) commitment from clinical leaders to initiate innovative changes to practice; (ii) potential for flexibility in service delivery (eg, variability in length or frequency of appointments, use of telehealth, involvement of nursing/allied health professionals in care) and (iii) the aim to include clusters across a spread of specialties.

Individual participants will include staff and patients who will contribute data to implementation outcomes. All staff working in the selected specialty areas during the study period (including medical staff, nursing and allied health staff, clerical staff and managers) will be invited to contribute to service reforms aligned with the intervention and be eligible to participate in focus groups. While some clinical specialties employ large numbers of sessional medical staff, we aim to include 4–8 participants per focus group for each clinic who are representative of key stakeholder groups and have detailed knowledge of clinic operations. For semi-structured interviews with patients, eligibility criteria will include the following: adult patients (or caregivers of children) who have been triaged as routine patients, recent attendance at a first appointment with a participating clinic; capacity to provide consent and sufficient oral communication capacity to participate in an interview (with an interpreter if required). Purposive sampling will be used with the aim of including a diverse range of participants.

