### Outcome measures

#### Effectiveness outcomes

Quantitative outcomes will be obtained from routinely collected healthcare data and auditing of health service processes. The primary outcome measure for effectiveness will be waiting, measured as time from initial referral to first appointment and the number of people on the waiting list (measured weekly). Secondary outcomes include the number of emergency department presentations and days admitted to the health service during the 6 months prior to and following the first clinic assessment to determine whether there is a relationship between improved specialist clinic access and other health service utilisation (outpatient services, emergency presentations and health service admissions). These data will be collected for a subgroup of patients attending the clinic for the first time within two of the pre- and post-implementation time blocks (darker shades in figure 1). Factors that may be covariates that impact on waiting times will also be recorded (demographic data, diagnosis and referral source).

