### Sample size

A minimum average of 400 referrals is expected to be received for each included specialty annually (100 per quarter), resulting in at least 700 patients across the pre- and post-implementation periods for each cluster (minimum total sample, n=5600). With four steps and eight clusters (two clusters per step), this stepped wedge design will be well powered to detect even small-to-moderate effect sizes. For a mean difference of 0.25 SD in waiting time and a conservative ICC of 0.1, with at least 60 referrals per cluster per 3-month time period (which is less than the pro-rata expected number annually), this design is powered at approximately 90% to sufficiently detect a difference at a 5% level of significance.^38
39^ Again, under conservative assumptions, power for detecting significant differences for our secondary outcomes (eg, an increase in the proportion of urgent patients seen within 30 days from 80 to 90%) exceeds 90%. Compared with our findings from STAT implementation in community outpatient services,^27^ our power and sample size assumptions are chosen conservatively to more than compensate for additional heterogeneity or other differences in the specialised clinic setting.

The sample size for quantitative implementation outcomes is based on the duration of the intervention and length of the waiting lists of the included services. The sample size for the qualitative analysis is considered feasible and expected to be sufficient to reach information power.

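### One clinic random effect in every model leaves out correlation that decays over time, so the primary test holds its 5% level only if that decay is absent

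*Protocol article*

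**What the plan says.** All places are in the protocol article.

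- **Random effects** (Analysis, Effectiveness): "A random effect for the clinic will be used for all models to account for clustering". This applies to every model. No cluster-by-period term, random time slope or autocorrelation structure is named.
- **Fixed effects** (same section): "time-point (time since trial start) and time since intervention as factor variables".
- **Small-sample correction** (same section): "the Kenward-Roger small-sample correction will be used for the df for inference of the fixed effects".
- **Other provisions** (same section): visual diagnostics, with transformations or robust estimators if needed; an indicator for notable disruptions, which may be confined to the affected clusters; and within-cluster time-series analyses as a sensitivity analysis.
- **Primary outcome** (Effectiveness outcomes): the wait between referral and first visit, together with list size, given as "the number of people on the waiting list (measured weekly").
- **Randomised unit** (Inclusion criteria): "the clinics operating under each specialty will collectively form one cluster in the trial".
- **Power** (Sample size): the effect size and correlation are set by "For a mean difference of 0.25 SD in waiting time and a conservative ICC of 0.1". The volume assumed is 60 referrals per cluster-quarter, and the claim made on that basis is that "this design is powered at approximately 90% to sufficiently detect a difference at a 5% level of significance". One ICC is given and no between-period correlation.

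**The concern.** A single cluster effect implies a constant correlation between any two patients of the same specialty, whatever the gap in time. Waiting times depend on backlog and staffing, which can shift within one specialty from quarter to quarter. The time-point factor removes only shifts shared by all eight clusters. Specialty-specific shifts that are left out of the model are treated as if they averaged out over patients, which they do not. The standard error of the intervention effect is then too small.

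List size is more exposed. A waiting list is a stock: this week's list is last week's plus arrivals minus departures. If weekly values are analysed with only a cluster effect, serially dependent values are counted as independent information.

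In both cases the error runs towards intervals that are too narrow and p-values that are too small, on both measures that make up the primary outcome.

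**Working it through.** **Inputs from the protocol article.** There are eight clusters in four pairs and 9 quarters (27 months; 31 March 2025 to 27 June 2027 is 117 weeks). The baseline is 2 quarters, a new pair starts every quarter, and each cluster has 2 implementation quarters outside the pre/post comparison. That leaves 7 analysed quarters per cluster, which matches the stated 700 patients at 100 per quarter, and 56 cluster-quarters in all. ICC is 0.1, effect 0.25 SD, with 60 (power basis) or 100 (expected) referrals per cluster-quarter.

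**Assumed, because not given.** CAC for waiting time, weekly autocorrelation for list size, and a two-sided test.

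**The plan's own figure.** Generalised least squares on cluster-quarter means with CAC 1, a common effect and a normal approximation gives power of 94.6%, 96.3% and 98.1% for layouts of 5, 6 and 9 periods with no transition. The stated 90% is approached only with ad hoc small degrees of freedom (for example 89.3% with 6 periods and 7 df). The layout described, with two implementation quarters excluded, gives SE 0.1336 and power Φ(0.25/0.1336 − 1.96) = Φ(−0.089) = 46%. This is at CAC 1, before any change to the random effects.

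**Size of the waiting-time test.** Set total variance to 1. The true components are ICC × CAC between clusters, ICC × (1 − CAC) between quarters within a cluster, and 1 − ICC between patients. The effect is estimated mainly within clusters, so to a close approximation

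(true SE / model SE)² ≈ [ICC(1 − CAC) + (1 − ICC)/m] / {[1 − ICC + ICC(1 − CAC)]/m}, and size = 2Φ(−1.96 × model SE / true SE).

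For m = 60 and ICC 0.1:

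- CAC 0.95: (0.005 + 0.0150)/0.01508 = 1.326; SE ratio 1.15; size 9%.
- CAC 0.9: (0.010 + 0.0150)/0.01517 = 1.648; SE ratio 1.28; size 13%.
- CAC 0.8: (0.020 + 0.0150)/0.01533 = 2.283; SE ratio 1.51; size 19%.

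The full sandwich variance on the 56 cluster-quarters agrees:

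| Setting | CAC 1 | 0.95 | 0.9 | 0.8 |
|---|---|---|---|---|
| ICC 0.1, 60 per quarter | 5.0% | 8.9% | 12.6-12.9% | 19.4-19.9% |
| ICC 0.1, 100 per quarter | 5.0% | 11.5-11.6% | 17.5-17.7% | 26.9-27.4% |
| ICC 0.05, 60 per quarter | 5.0% | 6.8% | 8.6-8.7% | 12.2-12.4% |
| ICC 0.01, 60 per quarter | 5.0% | 5.3% | 5.6-5.7% | 6.3% |

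The ranges reflect whether the fitted variances are set to the nominal ICC or to the values the misspecified model would absorb. Simulation with REML fits (1,500 runs per setting) gave 5.5%, 12.7% and 18.7% at CAC 1, 0.9 and 0.8 for ICC 0.1 and 60 per quarter. Replacing the common effect by time since intervention as a factor, as the plan does, gives nearly the same (12.7-19.5% at CAC 0.9-0.8).

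**Size of the list-size test, if weekly rows are modelled.** 117 − 26 implementation weeks leaves 91 counts per cluster. The true errors are AR(1) with parameter ρ, and the fitted model has a cluster effect, time factors and independent errors:

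- ρ 0.3: SE ratio 1.34; size about 14%.
- ρ 0.5: SE ratio 1.68; size about 24%.
- ρ 0.8: SE ratio 2.67; size about 46%.
- ρ 0.9: SE ratio 3.36; size 56%, or 54-61% depending on how time and the effect are coded.

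**Power once the cluster-by-quarter term is included** (60 per quarter, ICC 0.1, common effect, implementation quarters excluded): SE 0.1336, 0.1721 and 0.2032 at CAC 1, 0.9 and 0.8. Then Φ(0.25/SE − 1.96) = 46%, 31% and 23%.

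**The case against.** **The size depends on quantities the protocol does not give.** This stands. At CAC 1 the test holds 5%. The ICC of 0.1 is itself described as conservative, and at ICC 0.01 the inflation is slight (about 6%). A reader might infer that the trial's tests do run at 13-19%, or that a false positive is likely. The documents support neither: those figures need a CAC of 0.8-0.9, and even then the error rate without an effect is far below one half.

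**Measured weekly is a collection frequency, not a model.** This also stands. A reader might infer that 91 weekly rows per cluster enter the analysis as exchangeable. The protocol does not say so, the abstract ties the linear mixed model to waiting time, and quarterly aggregation would fit the text. The list-size figures are therefore conditional.

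**The plan is not blind to disturbances over time.** It has diagnostics, robust estimators, a disruption indicator that even names staffing issues, and within-cluster time-series analyses. So it would be wrong to say that it ignores the matter. But the first three are conditional and the last is a sensitivity analysis. None puts ordinary quarter-to-quarter or week-to-week correlation into the primary test. Robust standard errors with eight clusters are themselves unreliable.

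**Kenward-Roger protects against few clusters.** It does so under the fitted covariance. With one random effect the degrees of freedom for a mainly within-cluster contrast are large, and the missing component stays missing. A reader might also infer that it is meant for the binomial and negative binomial models; the text does not expressly assign it to them.

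**Clinic may simply mean specialty.** Probably so, since the Qualitative data section speaks of eight participating clinics. Read literally, though, it places the effect below the randomised unit, so the word should be fixed.

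**Conclusion.** The concern holds in conditional form. The protocol commits every model to one clinic random effect, and that model is valid at 5% only if the within-specialty correlation does not decay between quarters. At the plan's ICC of 0.1 and 60 per quarter, the true size rises from 5% to about 9%, 13% and 19% as CAC falls to 0.95, 0.9 and 0.8. For CAC 0.9-0.8 it is 9-12% at ICC 0.05, about 6% at ICC 0.01, and 17-27% at ICC 0.1 with the expected 100 per quarter. Weekly list counts, if modelled as weekly rows with the same effect, give about 14%, 24%, 46% and 54-61% at weekly autocorrelation 0.3, 0.5, 0.8 and 0.9. CAC and weekly autocorrelation are assumptions throughout. The direction is not in doubt: any decay makes the stated test anti-conservative, and none of the listed safeguards corrects the primary analysis for it.

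**What to change.** In the Effectiveness analysis section:

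1. Specify random effects for specialty (the randomised cluster) and specialty-by-quarter in the primary model, or a between-period correlation that decays with time. Replace clinic by specialty.
2. State how list size is analysed: AR(1) errors within specialty, or one mean per specialty-quarter.
3. Optionally, report as a check a permutation p-value over the 8!/(2!)⁴ = 40,320/16 = 2,520 possible allocations.

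In the Sample size section, give power over a stated range of CAC for the layout actually used.

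The first part costs analysis wording and some computing. The real price is wider intervals and lower stated power. For 0.25 SD at ICC 0.1 and 60 per quarter, with the two implementation quarters excluded, power is about 46% at CAC 1, 31% at 0.9 and 23% at 0.8. The fall from 46% is not caused by the new term; it reflects uncertainty that the single-effect model leaves out. The gap between 46% and the stated 90% comes from the layout and would remain under the current model.

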#### Implementation

Quantitative implementation outcomes, including the outcome of the waiting list audits, the ratio of demand to clinic capacity for new patients and indicators of change in patient flow, will be analysed descriptively. Qualitative data generated from staff will be mapped deductively to the domains of the Consolidated Framework for Implementation Research (CFIR). Rating rules for the CFIR and a cross-comparison analysis will be used to compare the experiences of different clinic teams.^42^ This method of analysis allows each comment made by participants to be coded in relation to its relevance to a subdomain of the CFIR and rated as ± according to whether the comment suggests a positive or negative influence of the factor on implementation.

Qualitative data generated from patients will be analysed using a thematic matrix analysis.^43^ Initially, the interview transcripts will be coded inductively line by line, then codes will be used to identify themes and subthemes. These themes will then be organised into a matrix to compare perceptions of patients who attended the clinic during the pre-implementation period and those who attended during the post-implementation period.

A cost of implementation and cost-effectiveness analysis will be completed from a health service perspective. A priori subgroup analysis of clinic patient types (urgent vs routine) will be completed as part of the economic evaluation. The cost of implementation will include two parts: (1) the cost of initial backlog reduction and (2) the cost of clinic operations. The cost of initial backlog reduction will be calculated by dividing the total cost by the incremental difference in the number of patients on the waitlist at the end of the pre-implementation period and the number of patients on the waitlist at 30-day post-implementation. The total cost of clinic operations will be calculated using quarterly audits throughout the trial to record all usual care costs (usual care staffing, capital and overhead costs) as well as any additional investment associated with the intervention, less the income derived from activity-based funding received by each cluster. A unit cost will be calculated by dividing the total cost for each cluster in each 3-month period by the number of new patients who receive a first appointment with a clinic within that cluster during that time. Each of these costs will be reported as a cost per cluster and as mean costs (with SD) across clinics. Costing at the service level will enable comparative efficiency measures such as the ratio of inputs to service output. The cost of implementation analysis will be presented as an overall cluster cost, as well as a cluster cost for the pre-implementation period and as a cluster cost for the post-implementation period.

To establish the incremental cost-effectiveness ratio (ICER), pre-implementation to post-implementation, cost differences will be divided by the percentage difference of urgent and routine referrals seen within 30 and 90 days, respectively, to determine the cost per 1% increase in the proportion of patients seen within these thresholds. ICERs will be determined by bootstrapping individual cost and effect data 5000 times, and this will be presented as an ICER value with 95% CIs and visually presented on a cost-effectiveness plane.

All cost data will be inflated to AUD$ 2026/2027 (final year of data collection) using the consumer price index and will take a health service perspective.^44^ Due to the nature of the economic evaluation planned, economic modelling will not be required. A discount rate will not be applied due to the limited time horizon and future economic impacts not being considered.

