### Intervention and implementation strategy

The intervention will consist of a suite of service redesign initiatives based on the STAT model. During the implementation period, staff within each cluster will be trained in the STAT model in workshops of 1–4-hour duration (tailored for teams and individuals according to prior knowledge of STAT and role within the service, with options for flexible delivery), led by investigators [name] and [name]. This training was developed at Eastern Health/La Trobe University and has been delivered to more than 1000 clinicians across Australia from more than 100 services over the past 4 years.^35^

Following training, the clinic staff will be guided through each of five steps of the STAT model: (i) analyse clinic supply and demand data, (ii) model supply and demand at the clinic, (iii) targeted interventions to address the existing backlog (using a comprehensive waiting list audit supplemented by targeted, short-term supply-side interventions), (iv) protect capacity for new patients to align with demand and (v) implement tailored strategies to enhance patient flow. Step 5 will incorporate enhanced clinic coordination, alongside other strategies that could include (but are not limited to) productivity improvements (such as reducing failure-to-attend rates), multi-disciplinary approaches to service delivery and partnerships with patients and primary care (table 1).

**Table 1 T1:** Key WaitLESS intervention activities and corresponding resources

Key activities	Resources provided
**Staff training** in the principles of the STAT model	Four-hour workshop training provided by members of the research team
**STAT Step 1:** Retrospective collection and analysis of clinic data—typical supply and demand over past 2 years	Support from research team/project manager
**STAT Step 2:** Model supply and demand; determine how much capacity needs to be protected for new patients to maintain flow at the rate of demand	Support from research team/project manager
**STAT Step 3**: Address existing backlog. Example activities: Comprehensive waitlist audit: cleaning the list, including checking for errors and calling/messaging patients to determine need Short-term increase in supply Grouping similar patients for targeted interventions	Clerical assistance for auditing Some funding for additional short-term clinic supply
**STAT Step 4:** Redesign clinic templates to align with demand	Support from research team/project manager

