#### Health economics data

During the 27-month study period, data for the cost of implementation analysis will be obtained from the following sources: (i) data extracts from clinic administrative and waiting list databases, (ii) audit of patient medical records and (iii) verbal reports obtained from clinic leaders through direct approach and semi-structured interviews. This costing data will be prospectively collected using a customised Excel spreadsheet at the end of each 3-month period (online supplemental file A details the data fields). The spreadsheet will capture 6-month pre-implementation, 6-month implementation and 6-month post-implementation of the STAT model (see figure 1). Cost-effectiveness analysis will include the cost of implementation data, as well as individual participant health service utilisation data, to determine the cost and tracking of patient waiting times to determine the effect.

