Acceptability, feasibility and appropriateness will be evaluated using qualitative data from staff and patients. Staff perspectives will be sought during the pre-implementation and implementation periods (perceptions of current state, views about the intervention and challenges/enablers for implementation) as well as 6 months after the commencement of the post-implementation period (perceived success or failure of the intervention, impact on patient care, staff workloads and job satisfaction and reflections on feasibility and appropriateness of the STAT model for specialist clinics). Patient perspectives of the clinic service will be sought from samples of patients who attend during the pre- and post-implementation periods.

The total cost of implementation will be considered in two parts: (i) Cost of initial backlog reduction (auditing and short-term additional supply) per patient removed from the waiting list and (ii) total cost of clinic operations during the pre- and post-implementation periods. The cost-effectiveness of the STAT programme will determine the incremental cost per percentage of urgent referrals seen within 30 days and routine referrals seen within 90 days, comparing usual care conditions to intervention conditions. Individual patient health service utilisation cost (outpatient services, emergency presentations and health service admissions) will be collected for the 6 months prior to their first clinic appointment and the first 6 months following this appointment, for patients under usual care conditions and for patients under intervention conditions (estimated n=800).

Outcome measures across all aspects of the trial are summarised in table 3.

**Table 3 T3:** Summary of outcome measures and data sources

	Routinely collected data	Consumer interviews	Staff focus groups	Prospective audits

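### The protocol is inconsistent on whether one-off backlog and set-up costs enter the ICER; its formula, read literally, leaves them out

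*Protocol article*

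**What the plan says.** Three sections of the protocol article bear on the ICER numerator.

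- **Data sources, Health economics data.** "Cost-effectiveness analysis will include the cost of implementation data, as well as individual participant health service utilisation data". On the period costed: "The spreadsheet will capture 6-month pre-implementation, 6-month implementation and 6-month post-implementation of the STAT model".
- **Outcome measures, Implementation outcomes.** Implementation cost has two parts. The first is backlog reduction (audit and temporary extra supply), expressed per patient taken off the list. The second is the "total cost of clinic operations during the pre- and post-implementation periods". The cost-effectiveness comparison is described as usual care against intervention conditions.
- **Analysis, Implementation.** "The cost of implementation will include two parts: (1) the cost of initial backlog reduction and (2) the cost of clinic operations". Operations cost is compiled "using quarterly audits throughout the trial to record all usual care costs" together with added investment, less activity-based funding income. Cluster cost is presented overall, for the pre period and for the post period. For the ICER, "pre-implementation to post-implementation, cost differences will be divided by the percentage difference of urgent and routine referrals seen within 30 and 90 days", with individual cost and effect data bootstrapped 5000 times.

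The Design section makes implementation a separate 6-month phase in each cluster, before post-implementation data begin. The intervention section and Tables 1 and 2 place training, the waiting list audit, template redesign and temporary extra capacity ("Some funding for additional short-term clinic supply") within the implementation process.

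**The concern.** The statement of intent and the formula do not match. One section says implementation costs, which include backlog reduction, belong in the cost-effectiveness analysis. The formula takes a difference between two periods that lie on either side of the phase in which most of the one-off spending occurs. The backlog cost has its own denominator, patients off the waiting list, and no step adds its total to the ICER numerator. No rule says how cluster-level set-up cost is assigned to the individual data being bootstrapped.

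An analyst who follows the formula would count the post-period gain in patients seen within 30 and 90 days without the spending that helped to produce it. The Design section says the results are meant to help providers decide and allocate funding. A service adopting STAT would have to pay for the audit, extra clinics and training, so whether these are in the cost per 1% gain is material.

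**Working it through.** **Step 1. Do the pre and post periods exclude implementation?** The stated sample size can test this.

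Inputs: trial dates 31 March 2025 to 27 June 2027, 6 months of control data, steps every 3 months, two clusters per step and 6 months of implementation (Design); 100 referrals per cluster per quarter, 700 per cluster and 5600 in total over the pre and post periods (Sample size).

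The dates span 819 days inclusive, and 819 / 91 = 9 quarters. Step s (1 to 4) has 1 + s pre quarters, 2 implementation quarters and 6 − s post quarters:

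| Step | Pre | Implementation | Post | Pre + post |
|---|---|---|---|---|
| 1 | 2 | 2 | 5 | 7 |
| 2 | 3 | 2 | 4 | 7 |
| 3 | 4 | 2 | 3 | 7 |
| 4 | 5 | 2 | 2 | 7 |

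With two clusters per step:
- pre: 2 × (2 + 3 + 4 + 5) = 28 cluster-quarters
- implementation: 2 × 8 = 16
- post: 2 × (5 + 4 + 3 + 2) = 28
- total: 72

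Per cluster, 7 × 100 = 700. Overall, (28 + 28) × 100 = 5600. Both stated figures are reproduced. Counting the implementation quarters would give 72 × 100 = 7200, which does not match. In this protocol, pre and post therefore exclude implementation.

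**Step 2. What does a literal pre-to-post difference skip?** It skips 16 / 72 = 22% of cluster-quarters. Of the 6 + 6 + 6 = 18 months in the costing spreadsheet, it skips 6 / 18 = 33%.

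**Step 3. Effect on the ICER.** Let Cpre and Cpost be the period costs, Cimpl the incremental implementation-period cost net of activity-based income (all on the same basis), and ΔE the gain in percentage points.

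- Literal formula: (Cpost − Cpre) / ΔE
- With the one-off cost: (Cpost − Cpre + Cimpl) / ΔE

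With r = Cimpl / (Cpost − Cpre) and both terms positive, the second is (1 + r) times the first, so the literal ICER is too low by r / (1 + r). The protocol gives no costs, so r is an assumption:

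| r (assumed) | Multiplier 1 + r | Literal ICER too low by |
|---|---|---|
| 0.25 | 1.25 | 20% |
| 0.5 | 1.5 | 33% |
| 1 | 2 | 50% |
| 2 | 3 | 67% |
| 3 | 4 | 75% |

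If Cpost − Cpre is zero or negative, the ratio r is not useful, but a positive Cimpl could turn an apparently cost-neutral or cost-saving result into a net cost.

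**The case against.** The strongest reply is that the protocol says these costs go in. Health economics data includes cost-of-implementation data in the cost-effectiveness analysis, and the Analysis section defines that cost to include backlog reduction. Added investment is recorded throughout the trial, and an overall cluster cost is reported. On this view the pre-to-post phrase names the two conditions compared, as Implementation outcomes does with usual care and intervention conditions, and is not an accounting window. Allocation detail may also sit in a full protocol or health economics plan that is not shown.

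Much of this stands. A reader might infer that the ICER definitely omits the one-off costs and so flatters STAT. The documents do not support that: omission is what the formula yields if taken literally, not a settled intention. The direction is conditional too. Costs are net of activity-based income, and extra clinics may earn some, so the sign of the net increment is not known. Staff hours do not measure the bias either, since they carry no price. The text of the intervention section also puts the coordinator in the pre and post periods, whereas Tables 1 and 2 say implementation and post. On either wording the coordinator is paid in the post period, so that recurring cost is in Cpost. Some project staff time is research, not health-service cost.

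What does not stand is that the matter is merely deferred. The article states a formula, and the formula conflicts with the article's own account of what the analysis contains. Recording a cost, or reporting it as a separate ratio, does not put it in the numerator.

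**Conclusion.** The concern holds as an inconsistency that should be resolved before analysis. The three sections disagree on whether one-off backlog and set-up costs enter the ICER, and the stated formula, followed literally, skips 22% of cluster-quarters (a third of the costed months). The cost per 1% gain would then be understated, provided the implementation-period cost net of activity-based income is positive. That is plausible but not shown. The 20% to 75% range rests wholly on the assumed ratio of 0.25 to 3 with both terms positive; it illustrates sensitivity and is not an estimate.

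**What to change.** In Analysis, Implementation, state that the ICER numerator includes the incremental health-service cost of the implementation period: backlog audit, short-term extra supply, training, coordinator and implementation support, excluding research-only costs and net of activity-based income. Align the wording in Health economics data and Implementation outcomes, and reconcile the coordinator's timing between the text and Tables 1 and 2.

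Prespecify one allocation rule, common to all clusters, for assigning this cost to the bootstrapped individual data. Spreading it over each cluster's own post period would be arbitrary: those periods run from 5 quarters down to 2, so the same outlay would weigh 5 / 2 = 2.5 times as heavily per quarter in step 4 as in step 1. State the time horizon too, since loading all set-up cost onto a short post period could count against STAT if the gains last.

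Report the ICER with and without the one-off component, so that readers can separate start-up from running cost.

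The cost is a change of wording and slightly more analysis, including separating research from implementation time. The spreadsheet already covers the 6-month implementation period, so no new costing period is needed. The ICER may look less favourable.
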